**Methods:**

A two-armed RCT was designed to compare an intervention group to a waiting list control group. Participants from the intervention group will receive TAO, an internet-based program for AjD composed of seven modules. TAO combines CBT and Positive Psychology strategies in order to provide patients with complete support, reducing their clinical symptoms and enhancing their capacity to overcome everyday adversity. Participants will also receive short weekly telephone support. Participants in the control group will be assessed before and after a seven-week waiting period, and then they will be offered the same intervention. Participants will be randomly assigned to one of the 2 groups. Measurements will be taken at five different moments: baseline, post-intervention, and three follow-up periods (3-, 6- and 12-month). BDI-II and BAI will be used as primary outcome measures. Secondary outcomes will be symptoms of AjD, posttraumatic growth, positive and negative affect, and quality of life.

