Given the impact and prevalence of AjD, we have developed TAO (*Trastornos Adaptativos Online*). TAO is the first online manualized intervention protocol for AjD developed for the Spanish-speaking population. The linear format of the program makes it possible to progressively start to solve the problematic situation. It is based on the CBT intervention protocol developed by Botella, Baños, and Guillén [31], which, to the best of our knowledge, is the first protocol specifically designed for AjD, showing efficacy in several studies [17, 32]. The aim of this study is to present the RCT that will be conducted to examine the effectiveness of TAO in reducing the distress and clinical symptoms of AjD, compared to a waiting list control group. Additionally, the level of patients’ acceptance and satisfaction with the intervention will be assessed.

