#### Waiting list control group

Participants on the waiting list group will be assessed before and after a period of 7 weeks. After completing a post-waiting period assessment, they will be offered the TAO program.

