### Data analyses

The statistical package IBM SPSS Statistics version 22.0 for Windows will be used for data analyses. Baseline differences between groups will be explored for continuous and categorical measures using both t-tests and chi-square tests. Repeated-measures ANOVAs will be used to assess within-group changes over time in primary and secondary outcome measures. Effect sizes will be estimated using Cohen’s d. Linear regression models will be used to study the effect of different variables (e.g., gender, age, and treatment expectations) on adherence and response to the intervention. Any participants who do not complete the post-intervention assessment will be considered drop-outs. On the other hand, the number of times each patient uses the program will be used as the measure of adherence.

Before analyzing the data, a review of state-of-the-art analytic methodology for RCT will be carried out in order to ensure the use of the most suitable statistical analyses. Finally, following SPIRIT and CONSORT guideline recommendations, both intention-to-treat and per-protocol analyses will be reported [34, 36].

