
Finally, personal growth achieved during the intervention period will also be assessed. According to WHO (1948), health is “A state of complete physical, mental and social well-being, and not merely the absence of disease or infirmity”. Huber et al. [63] also emphasize “the ability to adapt and to self-manage, in the face of social, physical and emotional challenges”. Consequently, the reduction in clinical symptomatology might be insufficient to achieve an optimal state of health. Improvements in coping strategies, however, might increase the ability to successfully overcome future challenges, without developing a sense of helplessness and/or AjD. Therefore, the main goal of TAO is to provide strategies to deal with current and future difficult situations, whether or not they can be resolved.

However, the study has limitations. The main limitation is the lack of an active treatment control group for comparison. However, because AjD is considered a transient condition [3], it is useful to explore whether brief interventions like TAO can prevent the chronification of this disorder and the development of more severe symptomatology. Moreover, given the lack of EBI for AjD, the comparison with a waiting list control group could be the first step in the validation of psychological treatments for this condition. Another limitation is that the decision about whether to include participants or not is based on the AjD diagnosis made using the *Diagnostic Interview for Adjustment Disorders*, which is not a validated instrument. The use of other diagnostic tools, such as the Adjustment disorder new model questionnaire (ADNM-20) [64], would have helped to corroborate the diagnosis. Unfortunately, there are no diagnostic instruments for AjD adapted and validated in Spanish for the beginning of RCT.

On the other hand, one potential difficulty in implementing the study might be the dropout rates. According to the literature, around 30% of those who start an ICBT do not complete the program. Preliminary results on the engagement in the BADI modular intervention for AjD showed a dropout rate of more than 80% in the intervention condition [29]. However, the inclusion of telephone support in the present study and the linear format of the TAO might improve the engagement of the patients who use it.

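### No between-arm outcome test is stated: the only test named for the primary and secondary outcomes is of within-group change, although the trial asks about TAO versus waiting list

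*Protocol article*

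**What the plan says.** **Question and design.** The abstract's Methods paragraph states: "A two-armed RCT was designed to compare an intervention group to a waiting list control group". The end of the Background gives the aim as "to examine the effectiveness of TAO in reducing the distress and clinical symptoms of AjD, compared to a waiting list control group". The Discussion repeats that comparison. The Sample size section assumes an effect size of 0.70, a 5% significance level and 80% power, and arrives at 26 per group, raised to 34 for dropout.

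**Analysis.** In the Data analyses section:

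- Baseline: "Baseline differences between groups will be explored for continuous and categorical measures using both t-tests and chi-square tests".
- Outcomes: "Repeated-measures ANOVAs will be used to assess within-group changes over time in primary and secondary outcome measures".
- Effect sizes: "Effect sizes will be estimated using Cohen’s d". The text does not say whether d is within or between groups.
- Regression: "Linear regression models will be used to study the effect of different variables (e.g., gender, age, and treatment expectations) on adherence and response". The examples do not include treatment arm.
- The section closes with a promised review of analytic methods before the data are analysed, and with intention-to-treat and per-protocol reporting.

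**Control arm.** The waiting list is assessed before and after 7 weeks. Then: "After completing a post-waiting period assessment, they will be offered the TAO program".

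**Course of the disorder.** The Discussion argues for brief interventions "because AjD is considered a transient condition". The Background says that, for the diagnosis, symptoms end within six months of the stressor or its consequences ending.

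**The concern.** The stated outcome analysis answers a different question from the one the trial was randomised and sized to answer. A within-group test asks whether scores in one arm moved. It does not ask whether they moved further than they would have without TAO. Participants enter while they meet diagnostic criteria, for a condition that the authors describe as transient. A fall in BDI-II and BAI can therefore come from the stressor passing, from regression to the mean, or from TAO, and a within-arm test credits all three alike.

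The same limit applies to follow-up. The waiting list is offered TAO after its 7-week assessment, so no untreated comparator is planned at 3, 6 and 12 months. The randomised contrast exists only at the post-intervention/post-waiting assessment, and no outcome test is named for it there.

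**Working it through.** **1. What the sample size is for.** Inputs from the Sample size section: d = 0.70, alpha 5% (sidedness not stated), power 80%, 26 per group. For two independent groups, n per group = 2(z_alpha + z_beta)² / d².

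- One-sided: 2(1.645 + 0.842)² / 0.49 = 25.2, so 26. Exact t power at 26 is 0.801. This reproduces the stated figure.
- Two-sided: 2(1.960 + 0.842)² / 0.49 = 32.0, so 33 (34 by exact t). Exact t power at 26 is 0.697.
- Paired within-group test with standardised change 0.70, two-sided: 19.

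The 26 is matched by a two-group comparison (one-sided) and not by a paired test within one group. Sidedness is a separate matter. What counts here is that the calculation is between groups and the named outcome test is not.

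**2. Whether anything else in Data analyses supplies the contrast.** The t-tests and chi-square tests concern baseline. Cohen's d is not tied to a comparison. The regressions concern predictors of adherence and response. Intention-to-treat and per-protocol define who is analysed, not what is compared. The methods review names no test. None states TAO against waiting list on an outcome.

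**3. What a within-arm test does when TAO has no effect.** Assumptions, none of them in the article: true treatment effect zero; both arms improve by the same amount delta (in SD units) between the two assessments; pre-post correlation r. The standardised change is dz = delta / √(2(1 − r)). The paired t-test has noncentrality dz·√n on n − 1 degrees of freedom, at two-sided 5%. For example, delta = 0.5 and r = 0.7 give dz = 0.5 / √0.6 = 0.645.

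Probability that the within-TAO change is significant:

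| delta (SD) | r | n = 24 | n = 26 | n = 34 |
|---|---|---|---|---|
| 0.2 | 0.5 | 0.156 | 0.165 | 0.205 |
| 0.2 | 0.7 | 0.228 | 0.245 | 0.310 |
| 0.3 | 0.5 | 0.291 | 0.313 | 0.397 |
| 0.3 | 0.7 | 0.444 | 0.476 | 0.592 |
| 0.5 | 0.5 | 0.650 | 0.688 | 0.808 |
| 0.5 | 0.7 | 0.857 | 0.885 | 0.955 |
| 0.7 | 0.5 | 0.907 | 0.929 | 0.977 |
| 0.7 | 0.7 | 0.989 | 0.993 | 0.999 |

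(34 is the recruited number per arm; 24 is about 34 × 0.7, after 30% dropout; 26 is the stated requirement.)

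**4. The between-arm test in the same settings.** With two time points, the group-by-time term is equivalent to a two-sample t-test on change. In 20,000 simulated trials per setting, at n = 26 and n = 34 over the same values of delta and r, it rejected in 4.8% to 5.2% of trials. Equal recovery in the two arms cancels out.

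**The case against.** **A condensed article.** A repeated-measures ANOVA in a two-arm trial can carry a group-by-time term, model terms are often left to an analysis plan, and a methods review is promised. A reader might infer from the text that TAO versus waiting list will not be tested, or that the randomisation will go unused. The article does not support that: it never says the within-group ANOVAs are the only analysis, and it poses the comparison repeatedly. What stands is narrower. This is not mere silence, because the article gives the purpose of its outcome test and gives it as within-group change, and nothing beside it names the contrast.

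**The decision rule.** A reader might also infer that effectiveness would be claimed when TAO is significant and the waiting list is not. The article states no such rule. With equal recovery and independent arms, that pattern has probability p(1 − p), which cannot exceed 0.25. It falls to about 0.02 or less at 0.7 SD with 34 per arm (for example 0.977 × 0.023 = 0.022). No weight is placed on it here.

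**Natural recovery is assumed.** The article also says that lack of treatment guidance often lets symptoms worsen, it mentions chronification, and its time limit for remission runs from the end of the stressor, which need not fall within 7 weeks. So improvement in both arms is plausible but not stated, and its size is unknown. This limits the illustration. It does not make a within-arm test able to identify a treatment effect.

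**Follow-up.** Maintenance of gains is one of the stated purposes of the later assessments, and within-group change is a natural description of it. A reader might take the Discussion as claiming that the trial can show prevention of chronification. It says only that this is useful to explore, so there is no claim to withdraw.

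**Conclusion.** The point holds in this form: for the primary and secondary outcomes the article states a within-group test and no between-arm test, against its own aim and its two-group sample size. Read as written, a significant fall in the TAO arm would not be evidence that TAO works.

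The size depends on assumptions. With no treatment effect, equal recovery of 0.2 to 0.7 SD, correlation 0.5 to 0.7 and 34 per arm, the within-TAO test is significant in roughly 20% to over 99% of trials, against about 5% for a between-arm test. The direction does not depend on the values chosen: any recovery shared by both arms pushes the within-arm rate above 5% and leaves the between-arm rate where it is. This should be corrected before analysis, because it concerns the test of the primary question.

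**What to change.** Replace the outcome sentence in Data analyses so that it specifies:

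- **Primary analysis:** the between-arm difference in BDI-II and in BAI at the post-intervention/post-waiting assessment, adjusted for the baseline score (ANCOVA, or the arm-by-time contrast of a mixed model), on the intention-to-treat set. Either model closes the gap.
- **Reporting:** the difference with its 95% CI, and Cohen's d defined as between-group.
- **Within-group change and the 3-, 6- and 12-month data:** labelled as uncontrolled description of maintenance, because the waiting list is offered TAO after 7 weeks.

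Fix this now instead of leaving the contrast to the methods review. The cost is one reworded paragraph. No new data are needed, since BDI-II and BAI are already collected at baseline. Adjustment may also gain precision: the variance factor for ANCOVA is 1 − r², so 0.75 at an assumed r of 0.5, against 1.0 for a post-only comparison and 2(1 − r) = 1.0 for change scores.

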### Randomization and blinding

Participants included in the study will have to sign the participation agreement without having a priori knowledge about their group assignment. Study researchers will also be blind to the group to which the assessed participants will belong. Once the online informed consent has been signed, an independent researcher will perform a “blocked randomization”, guaranteeing that the same number of participants are allocated to each condition (ICBT or WL). This allocation will be performed following a random number sequence generated by the Epidat 4.1 program.

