### Sample size

The sample size for the trial was calculated following the method described by Campbell, Julious, and Altman [37], and Freiman, Chalmers, Smith, and Kuebler [38]. G*Power 3 software [39] was used to facilitate power analysis.

Because there is no published research on the effectiveness of ICBT for the treatment of AjD, the sample size was calculated taking into account outcomes found in trials that used the BAI and BDI-II as measures of clinical change after an ICBT intervention in patients with clinical depression or anxiety disorder [40–42]. After reviewing the literature and adopting a more conservative approach, an effect size of .70 was assumed in the present study. Considering a significance level of 5% and a power of 80%, 26 participants in each group would be enough to detect the assumed difference. However, because the literature reveals dropout rates from ICBTs of around 30% [43], a sample of 68 participants will be recruited (34 per group).

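### Adherence is a count of program uses analysed by ordinary linear regression; with unequal predictor groups and a real difference, its 95% intervals can miss nominal coverage (minor, exploratory analysis)

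*Protocol article*

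**What the plan says.** The relevant text is in the protocol article under Data analyses. It defines the outcome: "the number of times each patient uses the program will be used as the measure of adherence". It also names the model: "Linear regression models will be used to study the effect of different variables (e.g., gender, age, and treatment expectations) on adherence", and on response to the intervention. No count model, transformation or robust standard error is mentioned for adherence. The same section promises that, before the analysis, "a review of state-of-the-art analytic methodology for RCT will be carried out in order to ensure the use of the most suitable statistical analyses", but it names no alternative for this outcome.

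The number of patients comes from Sample size: "a sample of 68 participants will be recruited (34 per group"). The same section notes that "the literature reveals dropout rates from ICBTs of around 30" per cent. The article gives no mean, variance or distribution for the number of uses, and no expected gender split.

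**The concern.** A number of uses cannot be negative and is often right-skewed, and its variance tends to rise with its mean. Ordinary linear regression pools the residual variance over all patients. If two groups of unequal size have different variances, the pooled figure is dominated by the larger group, while the uncertainty of the difference is often dominated by the smaller one. The standard error is then too small or too large, depending on which group varies more.

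At stake is the reliability of the intervals for who uses TAO more or less. An interval that is too narrow overstates certainty; one that is too wide can hide a real difference. The primary comparison of BDI-II and BAI is not involved.

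**Working it through.** The plan gives no figure for the adherence regression, so there is none to reproduce. The only relevant planned number is the arm size of 34, which follows from 26 × 1.3 = 33.8.

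**Inputs from the article.** Outcome: a count of uses. Model: linear regression. Patients: 34 in the TAO arm (about 24 if 30% are lost, 34 × 0.7 = 23.8; 68 if waiting-list patients who later take TAO are added).

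**Assumed inputs.** Negative binomial counts with shape k = 1, 2 or 4; splits of 8/26, 10/24 or 17/17; mean uses of 12 and 12, 18 and 10, or 7 and 14 (smaller group first).

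**Why the standard error is off.** With group variance v = m + m²/k:
- true variance of the difference: v1/n1 + v2/n2
- variance used by linear regression: s² × (1/n1 + 1/n2), with s² = [(n1 − 1)v1 + (n2 − 1)v2]/(n − 2)

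*Smaller group uses TAO more (8/26, means 18 and 10, k = 2).* v1 = 18 + 324/2 = 180; v2 = 10 + 100/2 = 60. True variance: 180/8 + 60/26 = 24.81. s² = (7 × 180 + 25 × 60)/32 = 86.25; variance used: 86.25 × 0.1635 = 14.10. Ratio of standard errors: √(14.10/24.81) = 0.754. Approximate coverage: 2Φ(2.037 × 0.754) − 1 = 87.5%.

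*Smaller group uses TAO less (8/26, means 7 and 14, k = 2).* v1 = 31.5; v2 = 112. True variance: 8.25. s² = (7 × 31.5 + 25 × 112)/32 = 94.39; variance used: 15.43. Ratio: 1.368. Approximate coverage: 99.5%.

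*Equal groups (17/17).* The two formulas coincide, so the ratio is 1.

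**Simulated coverage of the ordinary 95% interval, n = 34:**

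| Setting (assumed) | Coverage |
|---|---|
| No true effect | about 95% |
| 17/17, real effect | 94–95% |
| 8/26 or 10/24, smaller group higher (18 v 10) | about 85–90% |
| 8/26 or 10/24, smaller group lower (7 v 14) | 97–99% |
| 20/80 split, two-fold difference, k = 1 or 2 | 82–85% (smaller higher), 98–99% (smaller lower) |
| Poisson, no overdispersion | 89–98% |
| Continuous predictor, real slope | 92–95% if symmetric, 82–92% if skewed |

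More patients do not cure this. At n = 68, with a 20/80 split, k = 2 and the smaller group at twice the mean, coverage is 83.0%; HC3 errors raise it to 92.9%.

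**Missed differences.** With 8/26 and means 7 and 14, power is about 15% for linear regression against 36% for negative binomial (k = 1), and 39% against 59% (k = 2). In the other direction the order reverses: with a 20/80 split, k = 1 and the smaller group at twice the mean, linear regression rejects in 44% of runs against 37%.

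**A different distribution.** Suppose instead that leavers use TAO 1 to 3 times, completers follow a Poisson distribution with mean 12, and the predictor acts through dropout. With 8/26 and dropout of 10% and 40%, and leavers equally likely to use it 1, 2 or 3 times:
- group means: 0.1 × 2 + 0.9 × 12 = 11 and 0.4 × 2 + 0.6 × 12 = 8
- group variances: 0.1 × 0.67 + 0.9 × 12 + 0.09 × 100 = 19.9 and 0.4 × 0.67 + 0.6 × 12 + 0.24 × 100 = 31.5

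The group that uses TAO more now has the smaller variance, so the interval is slightly too wide. In simulation linear regression covers 97% here and negative binomial 99%, with power of 24% against about 11% to 12%. Across the mixture patterns tried, linear regression covers about 94% to 98%, and negative binomial without robust covariance 87% to 99%.

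**The case against.** The strongest reply is that the distortion depends on assumptions the article does not supply. TAO is a linear program of seven modules with weekly calls, so use may well cluster into early leavers and completers. In that pattern linear regression does about as well as a negative binomial model, or better. The distortion also needs both unequal groups (or a skewed predictor) and a real effect. Error structure is the kind of detail an article leaves to an analysis plan, and the promised methods review could deal with it.

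Much of this stands, and it rules out several stronger readings that a reader might infer:
- **That the direction of the error is predictable.** It is not; the mixture example reverses it, and the article gives no distribution of uses.
- **That negative binomial regression is better for any distribution of uses.** It wins when the data are negative binomial and the larger group has the higher mean; elsewhere it can lose coverage or power.
- **That false positives are inflated.** With no true effect, rejection stays near 5%.
- **That the protocol's statements on engagement and implementation rest on these results.** In the Discussion, implementation is tied to acceptability and satisfaction, which have their own scales. Engagement is discussed through dropout, which Data analyses defines separately as not completing the post-intervention assessment.

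What does not stand is that nothing has been fixed. The article names both the outcome and the model, and the general review neither replaces that model nor says when it would.

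**Conclusion.** The point holds as a minor one. The common-variance standard error is unreliable for this count when predictor groups are unequal and a real difference exists. The size is about 85% to 90% coverage if the smaller group uses TAO more and 97% to 99% if it uses TAO less. This rests on assumed negative binomial counts, 34 patients, splits of 8/26 or 10/24 and differences of roughly two-fold. More extreme splits widen the range to about 81% to 99%; a dropout mixture narrows it to about 94% to 98%. Linear regression still estimates the mean difference without bias, and the analysis is exploratory.

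**What to change.** For the adherence model only, state that linear-regression intervals will be heteroscedasticity-robust (for example HC3) or bootstrap. Also report a negative binomial model (log link, rate ratios, robust covariance) alongside it, or as the main model if the observed distribution of uses supports it. Robust intervals improve matters without being exact: in the 30/70 case they move coverage from about 87% to 92–94%, and a variance-robust analysis gave 89% to 97% across all the patterns tried.

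The cost is one sentence, slightly more analysis work, and a check that the named SPSS version offers the chosen option. Power falls in some configurations. When the smaller group uses TAO more, a correct interval in the worked example is about 1/0.754 = 1.33 times as wide as the ordinary one, so some apparent findings would go. The linear models for response to the intervention need no change on this ground.

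### The only outcome model named uses complete cases, so unless values are imputed or another model is used it cannot deliver the promised intention-to-treat analysis

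*Protocol article*

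**What the plan says.** All of the analysis text is in the Data analyses section of the protocol article. The model is given in one sentence: "Repeated-measures ANOVAs will be used to assess within-group changes over time in primary and secondary outcome measures". The software is SPSS 22. Drop-out is defined by the assessment, not by use of the programme: "Any participants who do not complete the post-intervention assessment will be considered drop-outs". Adherence is measured separately, by how often the programme is used. The section ends with a review of trial analysis methods to be done before the data are analysed, and with the promise that, "following SPIRIT and CONSORT guideline recommendations, both intention-to-treat and per-protocol analyses will be reported".

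The Sample size section gives the planning figures. On the size of the difference it says that "an effect size of .70 was assumed in the present study". The number needed is then stated as follows: "Considering a significance level of 5% and a power of 80%, 26 participants in each group would be enough to detect the assumed difference". This is raised to 34 per group (68 in all) on the ground that "the literature reveals dropout rates from ICBTs of around 30"%. The Discussion describes the same rate as programme non-completion: "around 30% of those who start an ICBT do not complete the program".

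The Waiting list control group section has those participants assessed before and after 7 weeks and then offered TAO.

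**The concern.** Three statements in one section do not fit together: a model that needs a complete set of scores, a drop-out definition under which the post-intervention score is missing, and an intention-to-treat promise. Classical repeated-measures ANOVA, as run in the SPSS general linear model procedure, deletes listwise anyone missing a visit in the model. A drop-out in the plan's sense has no post-intervention score, so as named the model cannot use that person.

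Three things are at stake. The result could carry an intention-to-treat label while resting on completers of the post-intervention assessment. Observed baseline data from drop-outs would be discarded. The arm comparison would also be open to bias if the people lost differ from those who stay, or if loss differs by arm. Differential loss is plausible, because only the TAO arm has a programme to abandon and the questionnaires run on the same online platform as that programme.

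**Working it through.** **Inputs from the documents.** Standardised effect 0.70, significance level 5% (sidedness not stated), power 80%, 26 per group needed, dropout allowance 30%, 34 per group recruited (all Sample size section). Equal allocation (Randomization and blinding section).

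**Reproducing the plan's figures.** With n = 2(z₁₋α + z₁₋β)² / d² per group:
- One-sided 5%: 2 × (1.645 + 0.842)² / 0.49 = 25.2, so 26. The t-based value is 25.94, also 26. This matches.
- Two-sided 5%: 2 × (1.960 + 0.842)² / 0.49 = 32.0, so 33. The t-based value is 33.02, so 34. This does not match 26.
- Dropout: 26 × 1.30 = 33.8, so 34, matches. Dividing instead gives 26 / 0.70 = 37.1, so 38.

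The stated 26 and 34 therefore reproduce as a one-sided test with multiplicative inflation. Power is shown both ways below because the text does not give the sidedness.

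**Who the named model would keep.** Assume that 30% in each arm lack the post-intervention assessment and nothing is imputed:
- Per arm: 34 × 0.70 = 23.8, about 24.
- Overall: 68 × 0.70 = 47.6, about 48 analysed and about 20 not.

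The stated requirement is 26 per arm. Power of a two-sample t-test at an effect of 0.70:

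| Per arm | One-sided | Two-sided |
|---|---|---|
| 24 | 0.77 | 0.66 |
| 26 | 0.80 | 0.70 |
| 34 | 0.89 | 0.81 |

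The last row is a ceiling that applies only if all 34 post-intervention scores are observed. No model recovers it when those scores are missing, which is why collecting them matters as well as choosing the model.

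**Bias, as illustration only.** The documents give no figure for how drop-outs differ from completers, and the direction depends on what is assumed.
- Suppose 30% of the TAO arm are lost with outcomes 0.3 to 0.5 SD worse than completers, and waiting-list loss is random. The overstatement is 0.30 × 0.3 = 0.09 SD to 0.30 × 0.5 = 0.15 SD, or 13% to 21% of 0.70.
- Suppose instead that TAO loss depends on the baseline score, with worse baseline meaning more loss (30% on average). Waiting-list loss is a random 30%, and baseline and post scores correlate 0.5. In a simulation of 4,000 trials with 34 per arm and a true effect of 0.70, the complete-case comparison of change averaged 0.57, an understatement. A comparison that used everyone's baseline (regression on baseline within arm, evaluated at the overall baseline mean) averaged 0.70.

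So completers-only analysis can err either way. Using all observed scores removes the part of the error that those scores predict, and no more.

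**The case against.** The strongest reply is that the article does not say observed cases only. ANOVA after imputation is compatible with intention to treat, and an article may leave missing-data handling to a fuller document. The planned review of methods also leaves room for a mixed model. This stands to the extent that the failure is conditional, and the absence of an imputation rule is not itself the point. It does not remove the mismatch. The one method that is named does not by itself deliver the analysis that is promised, and the review commits to nothing that keeps all randomised participants.

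A reader might also infer several stronger things that the documents do not support:
- *That 30% will miss the post-intervention assessment.* The rate is from the literature and the Discussion ties it to finishing a programme. Someone may stop TAO and still fill in the questionnaires. No rate is given for the waiting list. The plan does, however, use the figure to enlarge both groups.
- *That losses build up over five visits in both arms.* The waiting list is described as assessed before and after 7 weeks and then offered TAO, so the controlled comparison has two time points. The text does not say which visits enter the ANOVA.
- *That a completers analysis must overstate the effect.* No document gives the gap or its direction. The Discussion calls the disorder transient, so some people may leave because they have improved.
- *That intention-to-treat and per-protocol analyses would use the same people.* The article does not define the per-protocol set.
- *That the other online programme which "showed a dropout rate of more than 80% in the intervention condition" predicts loss here.* The Background attributes that rate to a modular, unguided format. TAO is linear and has telephone support.

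**Conclusion.** The point holds in conditional form. As named, the outcome model excludes everyone the plan calls a drop-out, so without imputation or another model the intention-to-treat analysis would be a complete-case analysis. If the plan's 30% applied to assessments equally in both arms, about 24 of 34 per arm would be analysed. That is below the stated 26, with power of 0.77 one-sided or 0.66 two-sided at an effect of 0.70. The count rests on that assumption, since the documents give no expected rate of missing assessments. The size and direction of any bias are unknown, and the SD figures above are illustrations under assumed gaps. It would be too strong to say that the plan has locked in a completers-only analysis, because the methods review leaves the choice open. That same openness means the primary intention-to-treat method is not fixed.

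**What to change.** In the Data analyses section, name the primary intention-to-treat analysis:
- Use a likelihood-based linear mixed model (the MIXED procedure in the SPSS package already named), with all randomised participants in their assigned arm and an arm-by-time term for the comparison of post-intervention with the end of the 7-week wait.
- Enter baseline and post-intervention scores both as outcomes. If baseline is only a covariate, anyone without a later score still contributes no outcome row and drops out.
- ANOVA or ANCOVA after multiple imputation is an acceptable alternative.
- Use the 3-, 6- and 12-month visits only to describe maintenance within the TAO arm, because the waiting list is offered TAO after 7 weeks.
- Add one delta-adjusted sensitivity analysis with drop-outs assumed worse. A mixed model does not remove bias from dropout that depends on unobserved outcomes.
- State that the post-intervention questionnaires go to everyone randomised, including those who stop the programme. The article does not say otherwise, but the intention-to-treat analysis depends on it.

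The cost is revised wording and a little more analysis work. It needs no new software, visits or participants.
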